**Fig. 2 Fig2:**
[figure not shown]
Schedule of enrollment, interventions and assessments (SPIRIT Figure)

At baseline, midline and endline the Hopkins Symptom Checklist (HSCL-25) will be administered to assess symptoms of depression and anxiety [23]. Functional dimensions of social support will be assessed with the Duke University–University of North Carolina Functional Social Support Questionnaire [24]. The Caregiver Knowledge of Child Development Inventory (CKCDI) will be administered to mothers/caregivers at baseline and midline [25]. At endline, we will also assess women’s empowerment with components of the Women’s Empowerment in Agriculture Index (WEAI) [26] and household food security with the Household Hunger Scale [27]. Maternal caregiver recall of child morbidities in the last two weeks (diarrhea, fever, and other morbidities) and any child hospitalizations during the study period will be assessed at midline and endline. All of these modules have been used in previous research studies in Tanzania.

In order to assess child development at midline and end line, trained female research nurses will administer a Tanzania adapted and Swahili translated version of the Bayley Scales of Infant Development III (BSID-III) [18, 28]. The cognitive, expressive language, receptive language, fine motor, and gross motor subscales will be administered. We will select two BSID-III nurse assessors based on quantitative performance evaluations after a three-week BSID-III training, led by experts from Boston, USA. BSID-III composite scores for each development domain will be reported. The BSID-III assessors will be blinded to the participant’s allocated trial arm. In order to assess drift and ensure continued quality of implementation, the study coordinator will conduct weekly field-based supervision of BSID-III data collection at midline and endline.

### Statistical analyses

All primary analyses will be conducted based on the intention-to-treat (ITT) principle. Women who moved to neighboring villages will be analyzed in the village originally randomized. Despite randomization, it is possible that there may be some degree of imbalance of baseline prognostic factors between randomized trials arms due to the small number of clusters. As a result, we will re-assess intervention effects after adjusting for factors that are potentially imbalanced between randomized trial arms. All analyses will account for village clustering. We will use linear regression models to assess the intervention effect on individual-level BSID-III domain scores, HAZ, and other secondary continuous outcomes. We will use log-binomial models to assess treatment effects on binomial outcomes. Linear mixed effects models and generalized linear mixed models will be used to assess longitudinal continuous and binomial outcomes, respectively. We will also examine effect modification of any treatment effect by predefined baseline variables: maternal age, maternal education, maternal/caregiver parenting knowledge, parity, household wealth, marital status, paternal residence in household, maternal depression, maternal social support, child age, child sex, number of CHW visits received, and number of CCTs received. We will also present analyses collapsing the CHW and CHW + CCT arms.

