### Sample size

Sample size calculations were based on randomization of 12 clusters with a cluster size of approximately 50 mother/caregiver-child pairs. We assumed a nominal Type I error rate (alpha) of 0.05 and assume a coefficient of variation of 0.49 an intra-cluster correlations of 0.01. We will have 80% power to detect a standardized mean difference (SMD) of 0.40 standard deviations in normalized anthropometric outcomes (HAZ, WHZ, WAZ), and 0.53 standard deviations of development z-scores. These are quite large effect sizes; however, this is a proof-of-concept trial and there is potential of the intervention package and the combination of CHWs and CCT to provide a sizable impact on child growth and development.

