### Randomization and interventions

Village clusters will be allocated in a 1:1:1 ratio to one of the three trials arms: (i) CHW, (ii) CHW + CCT, or (iii) Control. Stratified randomization will be done by a non-study statistician in Boston, USA according to a computer-generated randomization list with sequence blocks of three. Randomization will be stratified by semi-urban (six villages) and rural (six villages) villages to increase the likelihood of baseline balance.

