### Data collection

The schedule of trial enrollment, interventions, and assessments is presented in Fig. 2. Trained fieldworkers will conduct home interviews with mothers/caregivers at baseline, midline (9 months of follow-up) and endline (18 months of follow-up). The fieldworkers will be blinded to the randomized intervention arm. At baseline, all enrolled mothers/caregivers will be administered a standardized questionnaire including demographic and socioeconomic data. Child length/height, weight, head circumference, and MUAC will be taken in triplicate at baseline, midline and endline at the home. Child weight will be measured to the nearest 100 g using a digital scale (Seca, Hamburg, Germany). Length of children < 24 months of age will be measured to the nearest 0.1 cm with a length board (Seca) and height of children ≥24 months will be measured to the nearest 0.1 cm with the use of a portable stadiometer (Seca). Anthropometric z-scores will be calculated using the 2006 WHO child growth standards [22]. At baseline, midline and endline RCH cards will be used to assess antenatal care and child health clinic visit attendance.

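### The described analysis names neither the randomization stratum nor baseline HAZ as a covariate, and the only adjustment it states is chosen by observed imbalance

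*Protocol article*

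**What the plan says.** All references are to the protocol article.

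- **Randomization and interventions:** "Randomization will be stratified by semi-urban (six villages) and rural (six villages) villages to increase the likelihood of baseline balance". Allocation is 1:1:1 in blocks of three, so each arm gets two semi-urban and two rural villages.
- **Data collection:** "Child length/height, weight, head circumference, and MUAC will be taken in triplicate at baseline, midline and endline at the home". A baseline HAZ therefore exists for children already born. Under Trial population, pregnant women are also enrolled, and their children have none. BSID-III is given only at midline and endline.
- **Statistical analyses:** the co-primary outcomes are analysed by linear regression that accounts for village. The one adjustment described follows a remark that few clusters may leave prognostic factors unbalanced: "we will re-assess intervention effects after adjusting for factors that are potentially imbalanced between randomized trial arms". No candidates, trigger, or rule for which estimate prevails is given. The same paragraph does name variables in advance for effect modification, among them child age, child sex, maternal education and household wealth.

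**The concern.** A factor used to restrict randomization is normally carried into the analysis. If it is left out, any semi-urban/rural difference in outcome stays in the between-village residual, although the design has already removed it from the arm comparison. The standard error is then larger than the estimate's true variability, in a trial with only 12 clusters.

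Selection by imbalance does not repair this. Imbalance shows how the draw fell, not how strongly a factor predicts HAZ or BSID-III. The stratum is balanced by construction at village level, so only unequal village sizes could make it look imbalanced. The rule thus points away from the covariate that the design calls for. It also produces a second estimate for each co-primary outcome whose content depends on the data, and nothing says how to read a disagreement between the two.

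**Working it through.** **1. The plan's own figure.** Inputs from Sample size: 12 villages of about 50 dyads, hence four villages and about 200 dyads per arm; "We assumed a nominal Type I error rate (alpha) of 0.05" (taken as two-sided); for clustering, "assume a coefficient of variation of 0.49 an intra-cluster correlations of 0.01" (0.49 read as the CV of cluster size).

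- Design effect = 1 + ((0.49² + 1) × 50 − 1) × 0.01 = 1.610.
- SE of a two-arm difference = √(1.610 × 2/200) = 0.127.
- Noncentral t with 12 − 3 = 9 df and 80% power gives SMD 0.400 (power 0.801 at 0.40).

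This matches "We will have 80% power to detect a standardized mean difference (SMD) of 0.40 standard deviations in normalized anthropometric outcomes". The 9 df leave no room for a stratum term, so 0.01 works here as the overall ICC.

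**2. Largest stratum difference compatible with ICC 0.01.** Two equal strata that differ by d SD contribute d²/4 to between-village variance. Setting d²/4 ≤ 0.01 gives d ≤ 0.2. At d = 0.2 the stratum is the whole between-village variance.

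**3. CI half-width of a village-mean analysis.** With gamma-distributed sizes (assumption), k = 1/0.49² = 4.165 and the mean of 1/n is (1/50) × k/(k − 1) = 0.02632. The within-village part of a village mean's variance is 0.99 × 0.02632 = 0.02606.

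- With stratum: V = 0.02606 + (0.01 − d²/4), 8 df, t = 2.306.
- Without stratum: V′ = V + 12 × (d/2)²/9, 9 df, t = 2.262.
- Mean half-width = t × c × √(variance × 2/4). Here c corrects the mean of an estimated SD: 0.973 on 9 df and 0.969 on 8 df.

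| d (assumed) | V | V′ | Formula: without v with | Simulation: without v with |
|---|---|---|---|---|
| 0 | 0.0361 | 0.0361 | 0.295 v 0.300 | 0.294 v 0.299 |
| 0.1 | 0.0336 | 0.0369 | 0.299 v 0.290 | 0.297 v 0.287 |
| 0.2 | 0.0261 | 0.0394 | 0.309 v 0.255 | 0.310 v 0.255 |

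From the simulated values, omission widens the interval by 0.297/0.287 − 1 = 3% at 0.1 SD and 0.310/0.255 − 1 = 22% at 0.2 SD. It narrows it by about 2% if the strata do not differ.

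If a 0.2 SD difference is instead added on top of ICC 0.01 (total about 0.02), the half-widths are 0.345 v 0.299, and the unadjusted test rejects a true null 2.4% of the time.

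**4. Baseline HAZ.** If a share f of children has a baseline value and its correlation with endline is r (neither is given), residual variance is multiplied by 1 − f r². On 8 df the detectable SMD before this gain is 0.406. It becomes:

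- r = 0.3, f = 0.5: 0.406 × √0.955 = 0.397
- r = 0.5, f = 0.7: 0.406 × √0.825 = 0.369
- r = 0.7, f = 0.7: 0.406 × √0.657 = 0.329

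The gain over 0.400 runs from negligible to useful. It applies to HAZ only.

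**5. How often imbalance appears by chance.** For a covariate with village ICC 0.03 to 0.05 and a trigger of 0.2 SD (both assumptions, since the article states no trigger), some pair of arms differs by more than the trigger in 42 to 53% of simulated randomizations with four villages per arm.

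**The case against.** The strongest reply is that this is a condensed article and the analysis plan is not shown. Covariates of the primary model are often listed there, and naming linear regression excludes neither the stratum nor baseline HAZ. That stands against any claim that the stratum has been ruled out. It does not reach the imbalance rule, which the article states and which a later plan would have to override.

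Four stronger readings are tempting, and the documents do not support them:

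- **That imbalance adjustment replaces the main analysis.** The article calls it a re-assessment, so it is additional. The factors are also introduced as prognostic ones, though none is named.
- **That the intervals are too wide whatever the data show.** This needs the stratum to predict the outcome, which the article does not quantify. It also depends on how clustering is handled. With individual-level regression, cluster-robust errors and a normal reference (an assumption), simulation without the stratum gave null rejection of about 14% with no stratum difference, and about 10% and 7% with 0.2 and 0.3 SD added to ICC 0.01. Those intervals are too narrow, not too wide.
- **That the loss could be far larger, from stratum differences of 0.3 to 0.5 SD.** These imply d²/4 = 0.0225 to 0.0625 from the stratum alone, beyond the stated ICC of 0.01.
- **That age must be in the model because endline ages vary widely.** HAZ is age-standardized and the development outcome is powered on z-scores, so the gain from age is uncertain.

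**Conclusion.** The point holds as one of efficiency and pre-specification. The unadjusted estimate is not biased. The stated rule chooses covariates from the data and is unlikely to choose the stratum.

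For a village-level test with total ICC 0.01, leaving the stratum out widens the interval by about 3% at a 0.1 SD stratum difference and 22% at 0.2 SD. Including it needlessly widens the interval by about 2%. The trade therefore favours inclusion, but the benefit is conditional on a stratum difference that the article does not give.

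The 0.2 SD ceiling is only as firm as the ICC of 0.01. The stated "0.53 standard deviations of development z-scores" does not follow from that value: the same 9-df formula returns 0.53 only at ICC 0.03, which the article does not state. For development the ceiling is thus less certain. The benefit of baseline HAZ rests wholly on the assumed r and f, and BSID-III has no baseline to use.

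**What to change.** - Include the semi-urban/rural stratum as a covariate in the primary models for both co-primary outcomes.
- For HAZ, add baseline HAZ where measured, with an indicator (and a fixed fill-in value) for children not yet born at enrollment.
- Replace imbalance-triggered selection with a short prognostic list fixed before unblinding, for example child age, child sex, maternal education and household wealth.
- State which estimate is primary, and label any further adjusted analysis supportive.

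The cost is wording in the analysis plan and one cluster-level degree of freedom (9 to 8). No new data are needed, and follow-up was still ongoing at the date given under Trial status.

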**Methods/design:**

We will conduct a cluster-randomized controlled trial of a supply-side community health worker (CHW) delivered child health, nutrition, and responsive stimulation intervention alone and in combination with a demand-side conditional cash transfer (CCT) intervention to promote antenatal care and child growth monitoring attendance in rural Morogoro region, Tanzania. Twelve village clusters will be randomly assigned to one of the three trial arms: (1) CHW, (2) CHW + CCT, or (3) Control. Mothers (or another primary caregiver) residing in study villages are eligible for trial enrollment if they are currently pregnant or have a child < 1 year of age at the time of enrollment. For the duration of the trial, CHWs will visit households once every 4–6 weeks to deliver the intervention package and CCTs will be provided for documented antenatal care and routine child health and growth monitoring clinic visits. Participants will be followed-up at 9 months (midline) and 18 months (endline) post-randomization. The primary outcomes of the trial are child development assessed by the Bayley Scales of Infant and Toddler Development (BSID-III) and child height-for-age z-score. Secondary outcomes include a range of maternal, child and household outcomes.

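### With four villages per arm, the Protocol article names no inference method suited to so few clusters; ordinary cluster-robust standard errors would give a type I error of about 11–17% instead of 5%

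*Protocol article*

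**What the plan says.** All places are in the Protocol article.

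- **Design.** "Twelve village clusters will be randomly assigned to one of the three trial arms" (abstract, Methods/design). Allocation is 1:1:1, and "Randomization will be stratified by semi-urban (six villages) and rural (six villages) villages" (Randomization and interventions). That is four villages per arm, two per arm in each stratum.
- **Size.** The Sample size section assumes "randomization of 12 clusters with a cluster size of approximately 50 mother/caregiver-child pairs", an ICC of 0.01, a coefficient of variation of 0.49 and alpha of 0.05. It claims 80% power for 0.40 SD in anthropometric outcomes and 0.53 SD in development scores.
- **Analysis of continuous endline outcomes.** "We will use linear regression models to assess the intervention effect on individual-level BSID-III domain scores, HAZ" (Statistical analyses).
- **Analysis of binary outcomes.** "We will use log-binomial models to assess treatment effects on binomial outcomes".
- **Clustering.** "All analyses will account for village clustering". No variance estimator, working correlation, random effect, reference distribution, degrees of freedom or small-sample correction is named, and none is ruled out.
- **Mixed models.** The same section names linear and generalized linear mixed models for longitudinal outcomes only.
- **Few clusters.** The section raises the small number of clusters once, as a reason why baseline factors may be imbalanced and why adjusted estimates will be added.

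**The concern.** The co-primary outcomes are measured at endline, and single-level regression is the model named for them. Clustering is usually handled in such a model with a cluster-robust (sandwich) variance or GEE. Both rely on a large number of clusters. Here 12 village residuals support the whole variance estimate, and each pairwise contrast compares four villages with four. The sandwich is then biased downwards, and a normal reference ignores how imprecise it is.

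If the analysis follows that route, confidence intervals for BSID-III scores and HAZ would be too narrow, and false-positive findings would be two to three times as frequent as the nominal 5%. The covariate adjustment offered for imbalance does not repair this, because it acts on the estimate and not on the reference distribution.

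**Working it through.** **Inputs.** From the article: 12 villages, 3 arms, m = 50 per village, ICC 0.01, CV 0.49, alpha 0.05. Assumed: a two-sided test (sidedness is not stated), CV read as that of village size, and gamma-distributed village sizes in the simulations.

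**Step 1: reproduce the stated power (pairwise, 4 v 4 villages).**

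- Design effect = 1 + ((CV² + 1)m − 1) × ICC = 1 + ((0.2401 + 1) × 50 − 1) × 0.01 = 1.610.
- SE of the standardized difference = √(1.610 × 2 / (4 × 50)) = 0.1269.
- Noncentrality for 0.40 SD = 0.40 / 0.1269 = 3.152.

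| Reference | Power at 0.40 SD |
|---|---|
| Normal | 88.3% |
| t, 9 df (12 villages − 3 arms) | 80.1% |
| t, 8 df (also a stratum term) | 78.8% |
| t, 6 df (only the 8 villages compared) | 74.8% |

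Of these references, 9 df reproduces the stated 80%. The 0.53 SD figure does not follow from the printed ICC: 0.53 / 0.1269 = 4.18, which gives 95.9% with 9 df. It reaches 80.0% with an ICC of 0.03, which the article does not print (design effect 1 + 61.005 × 0.03 = 2.830, SE 0.1682, noncentrality 3.150).

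**Step 2: type I error under a true null.** Simulated for one active arm against control on a continuous outcome, with all 12 villages in the model, ICC 0.01, CV 0.49, nominal 5%. CR0 is the plain sandwich; CR1 is the sandwich with the usual degrees-of-freedom multiplier.

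| Method | No stratum term | With stratum term |
|---|---|---|
| Linear regression, CR1, t on 11 df | 11.1% | 12.6% |
| Linear regression, CR1, normal | 14.5% | 16.6% |
| Linear regression, CR0, normal | 16.1% | 18.3% |
| Village means, t on residual df (9 or 8) | 4.8% | 4.7% |

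These rows rest on 60,000 runs each. A separate simulation put the cluster-robust rows at 11.7–16.6% without and 13.2–18.5% with the stratum term, and village means at 4.8%. With equal village sizes and no stratum term, the three cluster-robust rows are 9.3%, 12.7% and 14.2%, so unequal sizes are not the main cause.

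From 4,000 runs per setting at ICC 0.01:

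- GEE with exchangeable correlation, sandwich and normal reference: about 15%.
- Random intercept, REML, Wald z: about 6–7%.
- Random intercept, ML, Wald z: about 8–10%.
- Random intercept, REML, t on residual village df: about 2.6–3.8%.

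**Step 3: can a permutation test serve instead?** For one pairwise contrast with two villages per arm per stratum there are C(4,2) × C(4,2) = 36 re-allocations. The smallest two-sided p is 2/36 = 0.056. If the randomization blocks of three are respected, there are 2⁴ = 16 swaps and the smallest p is 2/16 = 0.125. Neither can reach 0.05.

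**The case against.** The strongest reply is that the text is silent, not wrong. It commits to accounting for clustering, it is a condensed article, and the variance estimator and degrees of freedom are commonly left to an analysis plan, which is not shown here. This stands in part. A reader might infer that the trial has no small-sample correction, or that its type I error is 11–17%. The article supports neither: it excludes no correction, and those rates belong to uncorrected cluster-robust inference, a method that it does not name. A random-intercept model gives much less inflation, and a village-level t-test none.

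The reply does not dispose of the point. The article does choose a model family for the primary outcomes, keeps mixed models for another purpose, and takes up the small number of clusters while drawing only the consequence for baseline balance. Each default implementation checked with a normal reference exceeds 5%.

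It can also be said that the 0.40 SD figure fits a 9-df reference, so the planners probably allowed for few clusters. That is a fair inference, but no df is printed. It makes the gap in the analysis text easier to close; it does not close it. Nor can it be extended to both effect sizes, because 0.53 SD does not follow from the printed ICC and should not be cited in support.

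Three limits also stand. Only ICC 0.01 is the article's own value. The planned analysis that pools the two intervention arms compares eight villages with four, so the pairwise rates do not apply to it. No error rate was simulated for the log-binomial models; the same large-sample reliance applies there, but its size is not quantified.

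**Conclusion.** The point holds in conditional form. With four villages per arm, the Statistical analyses section fixes individual-level regression for the endline outcomes and names no inference method suited to so few clusters. If clustering is handled by ordinary cluster-robust or GEE standard errors, the type I error for a pairwise comparison of a continuous outcome is about 11–17% at the stated ICC and CV, and up to about 18% with a stratum term. A REML random intercept with a Wald z reference gives about 6–7%. Methods using between-village degrees of freedom hold the error at about 5% or below.

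This rests on a two-sided 5% test, CV read as variation in village size, and normally distributed outcomes. Both co-primary outcomes are affected, so the method should be fixed before the endline analysis; the article reports follow-up as still under way.

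**What to change.** State in the analysis section, or confirm in the analysis plan, that the primary contrasts use between-village degrees of freedom, and name one method:

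- a village-level (two-stage) analysis of village means, covariate-adjusted where planned, with a t reference on 9 df, or 8 df with the semi-urban/rural stratum term; or
- an individual-level REML random-intercept model with Kenward-Roger or Satterthwaite degrees of freedom.

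For binary outcomes, use the village-level analogue, or GEE with a bias-corrected sandwich and the same t reference. Do not substitute a pairwise permutation test, which cannot reach p < 0.05 here.

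**Cost.** Wording and standard software options. Intervals will be wider than under an uncorrected analysis: the reference change alone multiplies the half-width by 2.262 / 1.960 = 1.15 with 9 df. The mixed model may be somewhat conservative at ICC 0.01, as the REML result on residual df suggests. On the planning formula, power for 0.40 SD stays at 80.1% with 9 df and falls to 78.8% with the stratum term. That formula reflects size-weighted village means, so an unweighted version may be slightly less efficient when village sizes vary.

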#### CHW delivered child health, nutrition and responsive stimulation intervention

The CHW and CHW + CCT arms will receive the same supply-side CHW intervention. The project will recruit female CHWs living in the study villages catchment area who had completed a one-year government certified CHW program prior to being selected for the intervention. The government CHW curriculum included two semesters that each covered seven topics. The first semesters covered: (1) fundamentals of communication and customer service, (2) infection prevention and control, (3) management of health care facility, (4) computer application, (5) citizenship and gender, (6) management information systems, and (7) basic life support skills. The second semester covered: (1) fundamentals of social work, (2) disease prevention and control, (3) community-based reproductive, maternal and child health services, (4) community-based health promotion, (5) home-based care, (6) basics of entrepreneurship and life skills, and (7) health facility and community disease management. The main infant intervention components of the CHW curriculum include: 1) community-case management of under-5 childhood illness per Integrated Management of Childhood Illness (IMCI); 2) antenatal and postnatal pregnancy, delivery and essential newborn care counseling and danger signs identification; 3) family planning; 4) and emergency and routine referrals to facilities. The CHWs will be assigned to the study villages at the start of the trial. The salary for the CHWs is ~ 600,000 Tanzanian shillings (~$230) per month.

We will train the CHWs to deliver a responsive stimulation intervention that was integrated into the routine CHW home visit program. The responsive stimulation intervention is a Tanzanian and Swahili adapted version of the UNICEF and WHO Care for Development package [19]. The intervention includes communication of essential early childhood development knowledge, promotion of caregivers’ sensitivity and responsiveness, developmentally appropriate play and communication activities, toy making, and problem solving. Caregivers are provided the opportunity to try out responsive stimulation activities with their young child and receive feedback and coaching from the CHW. The CHWs will received a one-week training in September 2017 on the responsive stimulation intervention that included integrated classroom and practical sessions.

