CHWs will conduct home visits every 4–6 weeks throughout the trial follow-up period (18 months) to deliver the health, nutrition and responsive stimulation intervention package. The intended duration of the visit is 30–60 min per household, dependent on the health and well-being of the mother and child. One study coordinator will supervise the CHWs throughout the intervention. CHWs will met individually with the study coordinator biweekly to report visit completion. The study coordinator will accompany CHWs at least once per month to supervise home visits and provide feedback on intervention delivery. CHWs will also keep administrative records including the duration of home visits and the composition of messages delivered at each visit that will be reviewed by the study coordinator once a month. Monthly meetings will be held with all CHWs and the study coordinator to discuss progress and troubleshoot emerging challenges. A three-day refresher training on the responsive stimulation intervention will be conducted at trial midline (9 months). We will conduct in-depth qualitative interviews with each CHW at intervention completion to document their experiences and suggestions for improvement.

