#### Conditional cash transfer intervention

CHWs will also provide a demand-side CCT intervention to mothers/caregivers in the CHW + CCT arm. The conditions for the cash transfers are documented attendance of antenatal care or routine well-child health and growth monitoring clinic visits. Tanzania currently uses a focused antenatal care model with four visits; one before 16 weeks, at 20–24 weeks, at 28–32 weeks, and at 36 weeks gestation; postnatal child health and growth monitoring clinic visits are recommended to occur monthly until 2 years of age and then quarterly until 5 years [20, 21]. Reproductive and child health cards will be checked at CHW visits to document clinic visit attendance. CHWs will provide the CCTs for the duration of the follow-up period. Pregnant women will receive cash payments of 10,000 Tanzanian Shillings (~ $4.30) per antenatal care visit for up to four total visits. Mothers/caregivers will receive cash payments of 5000 Tanzanian Shillings (~ $2.15) per routine child health and growth monitoring clinic visit for up to one visit per month. Mothers/caregivers signed or provided thumbprints upon receipt of a cash transfer. The study coordinator will conduct random monthly spot-checks to ensure mothers/caregivers received CCTs as documented.

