#### Control arm

Villages in the control arm will receive no intervention and have access to existing clinic-based services. No quality improvement activities will be undertaken by the study team.

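### Two exposure counts that accrue after randomization (CHW visits and CCTs received) are listed as baseline effect modifiers; in most contrasts the interaction cannot be estimated, and otherwise it conditions on uptake

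*Protocol article*

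**What the plan says.** The Statistical analyses section announces: "We will also examine effect modification of any treatment effect by predefined baseline variables". Thirteen variables follow. Eleven describe the caregiver, household or child. The last two are "number of CHW visits received, and number of CCTs received".

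Other sections fix when these two counts arise, and in whom:

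- Visits: home visits are scheduled at 4- to 6-week intervals across the 18 months of follow-up. "The CHW and CHW + CCT arms will receive the same supply-side CHW intervention" (section on the CHW-delivered intervention).
- Cash: "CHWs will also provide a demand-side CCT intervention to mothers/caregivers in the CHW + CCT arm", and "CHWs will provide the CCTs for the duration of the follow-up period" (section on the conditional cash transfer intervention).
- Payment rule: "The conditions for the cash transfers are documented attendance of antenatal care or routine well-child health and growth monitoring clinic visits". Payments are capped at four antenatal visits and one child visit per month.
- Control: "Villages in the control arm will receive no intervention and have access to existing clinic-based services" (section on the control arm).

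Clinic attendance is itself secondary outcome (v) in the section on primary and secondary outcomes. The Statistical analyses section also states that primary analyses follow intention to treat, and that the two CHW arms will additionally be pooled.

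**The concern.** A baseline effect modifier is fixed before assignment, so treated and comparator participants with the same value can be compared and randomization protects the comparison. Neither count has that property. Each starts at zero for everyone, grows during follow-up, and can grow only in arms assigned to the relevant component.

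There are two consequences. Where the comparator count is always zero, the interaction does not exist as a separate parameter. Software will drop a term or return the slope of outcome on count within the exposed arm, which could then be reported as effect modification. Where the count does vary, the analysis compares households that took up more of the programme with households that took up less, and these may differ in ways that also affect growth and development.

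The trial is meant to inform policy on coordinating CHW and CCT programmes. A finding that more visits or more transfers go with more benefit would carry weight there. Labelled as predefined baseline effect modification, it would appear to have randomized support that it lacks.

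**Working it through.** The plan gives no figure on this point to reproduce. The check concerns timing and structure, followed by an illustration.

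**1. Timing.** Follow-up is 18 × 365.25 / 12 / 7 = 78.3 weeks. At 6-week spacing that is 78.3 / 6 = 13.0 visits, and at 4-week spacing 78.3 / 4 = 19.6. All of them fall after randomization, as do all cash transfers.

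**2. Which interactions exist.** Let T be the arm indicator, X the count, and fit

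E(Y) = b0 + b1·T + b2·X + b3·T·X.

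If X = 0 whenever T = 0, then T·X = X in every row. Only the sum b2 + b3 is determined, and it is the slope of outcome on count within the exposed arm. The interaction b3 has no separate value.

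The rank of the four-column design was checked numerically. It used 12 × 50 / 3 = 200 participants per arm, counts of zero where the article gives no exposure, and simulated counts elsewhere. Rank 4 is needed for b3 to be estimable.

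| Contrast | Rank, CHW visits | Rank, CCTs |
|---|---|---|
| CHW vs control | 3 | 2 |
| CHW + CCT vs control | 3 | 3 |
| Pooled CHW arms vs control | 3 | 3 |
| CHW + CCT vs CHW | **4** | 3 |

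Seven of the eight pairs fall short. For CCTs in CHW versus control the count is zero on both sides, so not even a slope exists.

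**3. Slope within an arm (illustrative).** Assumptions: no treatment effect; 200 participants; no clustering; a latent engagement trait U correlated ρ with the outcome; visits binomial out of 16 with logit probability 1.1 + 0.7·U; 1,000 replicates.

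| ρ (assumed) | Slope, SD of outcome per SD of visits | Significant at 5% |
|---|---|---|
| 0 | 0.00 | 4% |
| 0.1 | 0.07 | 18% |
| 0.2 | 0.15 | 60% |
| 0.3 | 0.23 | 91% |

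**4. The one estimable interaction (illustrative).** Visits in CHW + CCT versus CHW, under the same assumptions with 200 per arm. Entries are false-positive rates for b3.

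| ρ (assumed) | U drives visits equally in both arms | U drives visits in the CHW arm only |
|---|---|---|
| 0 | 6% | 3% |
| 0.2 | 4% | 21% |
| 0.3 | 5% | 43% |

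The rate stays near the nominal 5% when the link between engagement and visits is the same in both arms. It rises when the link differs, as it might if cash draws in households that would otherwise disengage.

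**5. Overlap with an outcome.** A transfer is triggered by documented clinic attendance. Up to the payment caps, the CCT count therefore largely tracks secondary outcome (v). It also depends on pregnancy status and child age at enrolment, because antenatal and child visits have different caps.

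**The case against.** The strongest defence is that these are secondary analyses in a self-described proof-of-concept trial, that the primary analyses are by intention to treat, and that most readers would take the two counts as a dose-response question. The first two parts stand: no primary estimate, sample size or error rate changes. The third does not, because the article calls the variables predefined, baseline and effect modifiers, and nothing in it recasts the two counts as dose or adherence analyses. This is a positive statement that is wrong, not detail left to a fuller document.

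It can also be said that the counts are not useless in every contrast. That is right: visits vary in both CHW arms, and bias in that interaction is a risk rather than a certainty.

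A reader might infer several stronger things that the document does not support:

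- **That the bias exceeds the detectable effect.** If visits correlated 0.2 with the outcome, the top and bottom thirds of a normal distribution would differ by 2.18 × 0.2 = 0.44 SD, and the article gives 0.40 SD as detectable for anthropometry. But the 0.2 is assumed, no analysis by thirds is planned, and a gap between extreme thirds within an arm is not comparable with a difference between arms. The detectable figure for development is 0.53 SD, which 0.44 does not reach.
- **That the CCT count is circular for all outcomes.** It is circular for clinic attendance. For height-for-age and the Bayley scores it is an adherence marker.
- **That child deaths would create a dose-response in the endline scores.** A child who has died has no endline score.
- **That the other eleven modifiers are all known at baseline.** Child age and sex are not known at enrolment for dyads enrolled during pregnancy. Unlike the two counts, however, they are not a tally of the intervention delivered.

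**Conclusion.** The concern holds as a secondary-analysis defect that should be corrected. The two counts are misclassified as baseline variables. Their interaction with arm is not estimable in 7 of 8 contrast-by-count pairs; in the eighth it is estimable but exposed to bias from conditioning on uptake. Any slope within an arm is a non-randomized adherence comparison.

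The classification error and the non-estimability follow from the article itself. The zeros assume that no CHW visits from outside the trial are counted in control villages, and the article mentions none. If some were counted, the visit interaction with control might become estimable, but the count would still be a post-randomization variable. The size of any adherence bias is not known: the correlations and the visit model above are assumptions, and the simulations ignore clustering. The intention-to-treat primary comparisons are untouched.

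**What to change.** Remove the number of CHW visits received and the number of CCTs received from the baseline effect-modifier list.

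If a dose question is wanted, state it in a separate sentence as an exploratory, non-randomized dose or adherence analysis within the exposed arms: visits within the CHW and CHW + CCT arms, and transfers within the CHW + CCT arm. Say that it is not effect modification by a baseline factor, and that the CCT count overlaps with clinic attendance.

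An instrumental-variable analysis is not needed for this correction. With zero exposure in the comparator, using arm as the instrument only rescales the intention-to-treat effect by mean exposure. For cash it would need assignment to act only through the transfers, which is doubtful when CHWs hand them out and visit uptake may change. Four villages per arm would also give it little support.

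The cost is one or two sentences in the analysis section, with no new data and no change to sample size. The article reports follow-up as still ongoing on 16 May 2019.
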